## PART 1 (ALL HEALTH WORKERS)

### SECTION 1: CHANGES AT WORK

To be administered by the study team

|                                                                                                                                                                                                                                                                                                                                                                                                                                |                                                                                                |
|--------------------------------------------------------------------------------------------------------------------------------------------------------------------------------------------------------------------------------------------------------------------------------------------------------------------------------------------------------------------------------------------------------------------------------|------------------------------------------------------------------------------------------------|
| 1. "Have you noticed any changes in the way patients are managed at this health center over the past few months?"

 
 1 = Yes
 2 = No 
 
 88 = Don't know
 99 = Refused to answer 
 
 
If yes, go to Qn 2. Otherwise, skip to the next section
 | 

 |
| 2. What do you think was the most significant or important change in the way patients are managed at this health center?

                                                                                                                                                                                                                |                                                                                                |
| 3. Why is this significant or important to you?

                                                                                                                                                                                                                                                                                         |                                                                                                |
| 4. What difference has this made in how patients are managed at this health center?

                                                                                                                                                                                                                                                     |                                                                                                |

## SSQ: HEALTH WORKERS (2)

|                               |                                     |                                                       |
|-------------------------------|-------------------------------------|-------------------------------------------------------|
| Health centre code
[ ] [ ] | Health Worker ID
[ ] [ ] [ ] [ ] | Date
[ ] [ ] / [ ] [ ] / [ ] [ ]
day month year |
|-------------------------------|-------------------------------------|-------------------------------------------------------|

## SECTION 2: SUPPLY MANAGEMENT

|                                                                                                                                                                    |         |                        |         |
|--------------------------------------------------------------------------------------------------------------------------------------------------------------------|---------|------------------------|---------|
| 1. 'Does this health center typically stock artemether-lumefantrine (Coartem or Lumartem)?'                                                                        | 1 = Yes | 88 = Don't know        |         |
|                                                                                                                                                                    | 2 = No  | 99 = Refused to answer | [ ] [ ] |
| If yes, go to Qn 2, otherwise skip to Qn 4                                                                                                                  |         |                        |         |
| 2. 'Have there been stock-outs of artemether-lumefantrine (Coartem or Lumartem) in the last 6 months?'                                                             | 1 = Yes | 88 = Don't know        |         |
|                                                                                                                                                                    | 2 = No  | 99 = Refused to answer | [ ] [ ] |
| 3. 'On a typical day, is the supply of artemether-lumefantrine (Coartem or Lumartem) adequate to treat the number of malaria patients seen at this health center?' | 1 = Yes | 88 = Don't know        |         |
|                                                                                                                                                                    | 2 = No  | 99 = Refused to answer | [ ] [ ] |
| 4. 'Does this health center typically stock rapid diagnostic tests (RDTs) for malaria?'                                                                            | 1 = Yes | 88 = Don't know        |         |
|                                                                                                                                                                    | 2 = No  | 99 = Refused to answer | [ ] [ ] |
| If yes, go to Qn 5, otherwise skip to Qn 7                                                                                                                  |         |                        |         |
| 5. 'Have there been stock-outs of RDTs in the last 6 months?'                                                                                                      | 1 = Yes | 88 = Don't know        |         |
|                                                                                                                                                                    | 2 = No  | 99 = Refused to answer | [ ] [ ] |
| 6. 'On a typical day, is the supply of RDTs adequate to manage the number of patients seen at this health center?'                                                 | 1 = Yes | 88 = Don't know        |         |
|                                                                                                                                                                    | 2 = No  | 99 = Refused to answer | [ ] [ ] |
| 7. 'On a typical day, is the supply of other drugs adequate to treat the number of patients seen at this health center?'                                           | 1 = Yes | 88 = Don't know        |         |
|                                                                                                                                                                    | 2 = No  | 99 = Refused to answer | [ ] [ ] |
| 8. 'On a typical day, does this health center have adequate equipment and supplies to manage patients?'                                                            | 1 = Yes | 88 = Don't know        |         |
|                                                                                                                                                                    | 2 = No  | 99 = Refused to answer | [ ] [ ] |
| 9. Please provide any additional comments about supply of drugs and other supplies at this health center.                                                          |         |                        |         |

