## SECTION 5: PATIENT MANAGEMENT

|                                                                                                                                                |                                          |                                           |         |
|------------------------------------------------------------------------------------------------------------------------------------------------|------------------------------------------|-------------------------------------------|---------|
| 1. "Is it possible to test patients for malaria at this health center?"
If YES, go to Qn 2, otherwise skip to Qn 5            | 1 = Yes
2 = No                        | 88 = Don't know
99 = Refused to answer | [ ] [ ] |
| 2. 'What tests for malaria can be done at this health center?'                                                                          | Read out each test and indicate for each |                                           |         |
|                                                                                                                                                | 1 = Yes
2 = No                        | 88 = Don't know
99 = Refused to answer |         |
| [ ] Microscopy (blood smear)                                                                                                                   |                                          |                                           |         |
| [ ] Rapid diagnostic test for malaria                                                                                                          |                                          |                                           |         |
| [ ] Other (describe) _____                                                                                                                     |                                          |                                           |         |
| 3. "Do you usually test patients for malaria before giving antimalarial treatment?"
If NO, go to Qn 4, otherwise skip to Qn 5 | 1 = Yes
2 = No                        | 88 = Don't know
99 = Refused to answer | [ ] [ ] |

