| 5. "What treatment should be given to patients with uncomplicated malaria?"

Record all answers given                                   | 1 = Artemether-lumefantrine (Coartem/Lumartem)
2 = Artesunate + amodiaquine
3 = Dihydroartemisinin-piperaquine (Duocotexcin)
4 = Any artemisinin-based combination therapy
5 = Quinine
6 = Chloroquine + sulfadoxine-pyrimethamine (Homapak)
77 = Other _____
88 = Don't know
99 = Refused to answer                                                                                                                                               | 
[ ][ ]

[ ][ ]

[ ][ ]

[ ][ ]

[ ][ ] |
| 6. 'Are you usually able to provide this treatment to your patients with uncomplicated malaria?'
If NO, go to Qn 7, otherwise skip to Qn 8 | 1 = Yes
2 = No                                                                                                                                                                                                                                                                                                                                                                                                                                                          | 88 = Don't know
99 = Refused to answer

[ ][ ]            |
| 7. "If not, why?"

Record all answers given                                                                                             | 1 = The drug is often out of stock
2 = The patients can't afford to buy
77 = Other _____
88 = Don't know
99 = Refused to answer                                                                                                                                                                                                                                                                                                                                | 
[ ][ ]

[ ][ ]                                           |

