## SECTION 2: SUPPLY MANAGEMENT

|                                                                                               |                                                                |        |
|-----------------------------------------------------------------------------------------------|----------------------------------------------------------------|--------|
| 1. 'Does this drug shop typically stock artemether-lumefantrine?'                      | 1 = Yes    88 = Don't know
2 = No    99 = Refused to answer | [ ][ ] |
| If yes, go to Qn 2, otherwise skip to Qn 5                                             |                                                                |        |
| 2. 'Is artemether-lumefantrine available today?'                                       | 1 = Yes    88 = Don't know
2 = No    99 = Refused to answer | [ ][ ] |
| 3. 'Have there been stock-outs of artemether-lumefantrine in the last 6 months?'       | 1 = Yes    88 = Don't know
2 = No    99 = Refused to answer | [ ][ ] |
| 4. 'Does this drug shop stock 'Green Leaf' artemether-lumefantrine supported by AMFm?' | 1 = Yes    88 = Don't know
2 = No    99 = Refused to answer | [ ][ ] |

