**SECTION 4: PATIENT MANAGEMENT**

1. "What treatments do you most commonly recommend for children with fever?"

*Record all answers given*

- 1 = Artemether-lumefantrine (Coartem/Lumartem) [ ] [ ]  
 2 = Chloroquine + sulfadoxine-pyrimethamine (Homapak) [ ] [ ]  
 3 = Quinine [ ] [ ]  
 4 = Paracetamol (Panadol) [ ] [ ]  
 77 = Other \_\_\_\_\_ [ ] [ ]  
 88 = Don't know [ ] [ ]  
 99 = Refused to answer [ ] [ ]

2. "What treatments do you most commonly recommend for adults with fever?"

*Record all answers given*

- 1 = Artemether-lumefantrine (Coartem/Lumartem) [ ] [ ]  
 2 = Chloroquine + sulfadoxine-pyrimethamine (Homapak) [ ] [ ]  
 3 = Quinine [ ] [ ]  
 4 = Paracetamol (Panadol) [ ] [ ]  
 77 = Other \_\_\_\_\_ [ ] [ ]  
 88 = Don't know [ ] [ ]  
 99 = Refused to answer [ ] [ ]

3. "What treatments do you most commonly recommend for a patient with uncomplicated (simple) malaria?"

*Record all answers given*

- 1 = Artemether-lumefantrine (Coartem/Lumartem) [ ] [ ]  
 2 = Artesunate + amodiaquine [ ] [ ]  
 3 = Dihydroartemisinin-piperaquine (Duocotexcin) [ ] [ ]  
 4 = Any artemisinin-based combination therapy [ ] [ ]  
 5 = Quinine [ ] [ ]  
 6 = Chloroquine + sulfadoxine-pyrimethamine (Homapak) [ ] [ ]  
 77 = Other \_\_\_\_\_ [ ] [ ]  
 88 = Don't know [ ] [ ]  
 99 = Refused to answer [ ] [ ]

4. Please provide any additional comments about patient management at this drug shop.

SSQ: PRIVATE DRUG SHOPS (5)

|                |              |                          |
|----------------|--------------|--------------------------|
| Drug shop code | Provider ID  | Date                     |
| [ ][ ]         | [ ][ ][ ][ ] | [ ][ ] / [ ][ ] / [ ][ ] |
|                |              | day month year           |

SECTION 5: ADDITIONAL COMMENTS

Please use this space to provide any other comments

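### The health-worker questionnaire names artemether-lumefantrine one to three times before its open question on malaria treatment, so that answer is cued to an extent that may differ by arm

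*Supplement*

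**What the plan says.** Section 5.7 gives the semi-structured questionnaire to up to 10 health workers in each ACT PRIME arm. Part 1 of Appendix U is marked for administration by the study team; only Sections 6 to 8 are marked as self-filled. The sections are printed in a fixed order.

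Section 2 (Supply management) comes early:
- Q1, to every respondent: "Does this health center typically stock artemether-lumefantrine (Coartem or Lumartem".
- The skip rule after Q1: "If yes, go to Qn 2, otherwise skip to Qn 4".
- Q2, only after a yes: "Have there been stock-outs of artemether-lumefantrine (Coartem or Lumartem) in the last 6 months".
- Q3, only after a yes, asks whether on a typical day "is the supply of artemether-lumefantrine (Coartem or Lumartem) adequate to treat the number of malaria patients seen at this health center".

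Section 5 (Patient management) comes later. Its Q5 asks "What treatment should be given to patients with uncomplicated malaria". The interviewer is to note every answer offered, and code 1 is artemether-lumefantrine (AL) with the same two brands. Q6 asks whether the worker can usually provide the treatment just named, and Q7 asks why not. By contrast, Section 5 Q2, on malaria tests, carries the instruction "Read out each test and indicate for each".

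Section 7.1 says categorical variables from this questionnaire will be compared by chi-square or Fisher's exact test at two-tailed 0.05. Section 5.7 says the form is a draft to be piloted and refined if necessary; question order is not mentioned.

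**The concern.** An open question about which treatment should be given is informative only if the respondent has not just been offered an answer. Here the interviewer supplies a drug name, with brands, earlier in the same sitting, and at Q3 presents it as what malaria patients are treated with. Someone who would have named another drug, or none, now has a ready reply.

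Q6 and Q7 depend on Q5. A cued reply changes which drug the worker is then asked about providing, and so changes the meaning of the stated reasons for not providing it.

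The item is put to both arms and falls under the Section 7.1 tests, so a reader of the results would naturally treat a difference, or its absence, as evidence about the intervention. Health-worker in-depth interviews are held in the intervention arm only (Table 4.1), so the later interviews of PROCESS offer no unprompted answer from standard-care workers to set against this one.

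**Working it through.** **Plan's own figure.** The maximum of 30 semi-structured questionnaires is 10 intervention health workers + 10 standard-care health workers + 10 drug shops = 30. It reproduces. The documents give no expected proportion, effect size or power for any item.

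**Count of mentions before Section 5 Q5.** Section 1, Sections 3 and 4, and Section 5 Q1–Q4 do not name AL. Section 2 gives 1 mention if Q1 is not yes, and 1 + 2 = 3 if it is. The Section 5 skip rules bring every respondent to Q5.

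**Is Q5 meant to be unprompted?** Section 5 Q2 says explicitly that its options are to be read out. Q5 has no such instruction. The natural reading is that Q5 is unprompted, though the form does not say so.

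**Direction.** Let p be the share who would name AL without a cue, and c the share of the remainder converted by it. The observed share is p + c(1 − p). All values of p and c below are assumptions.

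*Same c in both arms.* The difference becomes (1 − c)(p_HFI − p_SC), which is always smaller. With p = 0.90 and 0.50 (uncued difference 0.40):

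| c | HFI | Standard care | Difference |
|---|---|---|---|
| 0.25 | 0.925 | 0.625 | 0.30 |
| 0.50 | 0.950 | 0.750 | 0.20 |
| 0.75 | 0.975 | 0.875 | 0.10 |

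*Different c.* The difference grows whenever c_HFI(1 − p_HFI) exceeds c_SC(1 − p_SC). A larger c_HFI is possible because a yes at Section 2 Q1 triples the mentions and, under Section 5.10, ACT PRIME provides AL to the intervention centres.

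| Uncued p, HFI / SC | c, HFI / SC | Observed, HFI / SC | Difference, uncued → observed |
|---|---|---|---|
| 0.80 / 0.50 | 0.75 / 0.25 | 0.950 / 0.625 | 0.30 → 0.325 |
| 0.80 / 0.50 | 0.50 / 0.10 | 0.900 / 0.550 | 0.30 → 0.35 |
| 0.50 / 0.50 | 0.75 / 0.25 | 0.875 / 0.625 | 0 → 0.25 |
| 0.90 / 0.50 | 0.75 / 0.25 | 0.975 / 0.625 | 0.40 → 0.35 |

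The last row shows that when intervention workers are already near the ceiling, even a stronger cue in their arm leaves the difference smaller. That is the more plausible case after training.

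**How much rests on the item.** At 10 per arm one respondent is 10 percentage points. By Fisher's exact test, significance needs a split such as 10/10 against 5/10 or fewer, or 9/10 against 3/10 or fewer. Only a very large difference could be shown in any question order.

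**The case against.** **The item is not an endpoint.** Section 5.7 gives the questionnaire's purpose as contextual factors, perceptions and impacts. Health-worker knowledge scores are a separate ACT PRIME outcome (Table 1.1), and Section 4.5.1 sends quantitative assessment of hypothesised impacts to existing ACT PRIME tools wherever possible. This stands and limits the severity. It does not uncue the answers to Q5–Q7, which would still be tabulated and tested.

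**There may be little left to cue.** Section 5.3.4 targets the in-charges of facilities, and National Medical Stores also supplies AL (Section 5.10). Uncued shares could be high in both arms. The documents neither support nor exclude this, so no size should be claimed.

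**The form will be piloted.** True, and that is the place for the edit. But a pilot run in one fixed order cannot reveal an order effect.

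A reader might also infer three stronger things, none of which the documents support:
- *The arm difference is necessarily biased towards zero.* This requires equal cueing or a near-ceiling intervention arm. The skip rule and the AL supply to intervention centres mean neither can be assumed.
- *Naming RDTs in Section 2 spoils the testing questions in the same way.* Section 5 Q2 reads the tests out by design, and Q1 and Q3 are closed yes/no items.
- *Appendix V inflates the share of drug shops reporting AL.* It does open its supply section with "Does this drug shop typically stock artemether-lumefantrine" and an AL brand list before asking "What treatments do you most commonly recommend for children with fever". But it also prompts for other artemisinin combinations and, where other malaria drugs are stocked, for a list including chloroquine and quinine, several of which are competing answer codes. A push towards AL in particular is not established, and the plan describes no arm comparison for drug shops.

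**Conclusion.** The cue is real and can be read off the form: one mention of AL for every respondent, three where the centre stocks it, all before an apparently unprompted question whose first code is that drug. Q5 in Appendix U, and Q6–Q7 which hang on it, are affected. Shrinkage of any arm difference is likely but not certain; under unequal cueing the difference could be preserved, enlarged or created. No size can be derived, because the documents give neither uncued shares nor any measure of cue strength, and the illustrative proportions above are assumptions. The conclusion also assumes that Q5 is meant to be unprompted and that the printed order is followed. Severity is minor: a supporting item, at most 10 respondents per arm, in a draft form.

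**What to change.** In Appendix U, ask Section 5 Q5–Q7, or the whole of Section 5, before Section 2, and add an interviewer instruction that the Q5 answer codes are not to be read out. Leave the read-out instruction at Section 5 Q2 as it is. Skip instructions and section numbers need updating to match.

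Optionally, in Appendix V, ask Section 4 before Section 2 so that no drug is named before the recommendation questions. This is good practice and does not depend on the present order favouring any one drug.

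The cost is a reordering of draft forms before piloting, with no added items, interview time or staff. If data have already been collected in the printed order, report Q5–Q7 as prompted answers, tabulate Q5 by the Section 2 Q1 response within arm, and do not present the arm comparison as a measure of unprompted treatment knowledge.

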## SECTION 3: STAFFING

|                                                                                                                           |                               |                        |
|---------------------------------------------------------------------------------------------------------------------------|-------------------------------|------------------------|
| 1. "How many full-time staff members are stationed at this health facility?"                                              | Indicate number of staff      | [ ] [ ]                |
| 2. "On a typical day, how many full-time staff members are available to work?"                                            | Indicate number of staff      | [ ] [ ]                |
| 3. "How many volunteers are stationed at this health facility?"                                                           | Indicate number of volunteers | [ ] [ ]                |
| 4. "On a typical day, how many volunteers are available?"                                                                 | Indicate number of volunteers | [ ] [ ]                |
| 5. "On a typical day, are the staff available at this health center adequate to manage the number of patients attending?" | 1 = Yes                       | 88 = Don't know        |
|                                                                                                                           | 2 = No                        | 99 = Refused to answer |
| 6. Please provide any additional comments about staffing and use of volunteers at this health center.                     |                               |                        |

